### **Questionnaires**

The Perceived Stress Scale 10 (PSS10) is used to assess subjective stress burden. The SF-12 is a questionnaire for measuring health-related quality of life. It is a shortened version of the SF-36 and includes questions on physical functions and limitations, pain perception, general health status, vitality, social and emotional limitations and psychological distress. The EQ-5D-5L is additionally collected to obtain a more comprehensive picture of quality of life.

Resilience is assessed using the Brief Resilience Scale (BRS-D). The Somatic Symptom Scale (SSS) provides information on experienced somatic symptoms.

To assess psychological structure, the short version of the OPD Structure Questionnaire (OPD-SFK) is used. The questionnaire is based on the manual of Operationalized Psychodynamic Diagnostics (OPD-2) and is used for self-assessment of central structural abilities, particularly in the areas of self- and other-perception, control ability, emotional regulation and relationship formation. The short version enables an economical yet valid assessment of structural levels of functioning in the clinical context with 12 items. The scales show good internal consistency as well as criterion-related validity in various patient populations.

A stable structural level is considered a central prerequisite for healthy stress processing, as it significantly influences the ability for self-regulation in stressful situations.

At baseline, a dietary history is taken using the NutriMental Screener to gain insight into eating habits and nutritional status.

Food Frequency Items are recorded both at baseline and at follow-ups to document dietary changes and compliance with dietary recommendations.

To evaluate patient satisfaction in the specialized clinic, questionnaires are used that have been adapted from those of other clinics at LKH Graz. These include, among other things, questions on satisfaction with organization/processes, professional competence/care, tone of interaction/behavior toward patients, as well as open questions on overall impression and suggestions for improvement.

Both patients and treating physicians are asked to assess the patients' health literacy on a scale from 1 (very low) to 10 (very high) at all assessment time points.

In addition, we collect the following clinical and demographic parameters: age, sex, height, BMI, medication, smoking behavior, chronic organic diseases, psychiatric diagnosis, educational status, employment/employment level.

Completion of the baseline questionnaires takes approximately 20 minutes, and completion of the follow-up questionnaires approximately 10–15 minutes.

### Standard Laboratory

Blood samples will be taken at baseline and then every three months during the regular follow-up appointments by staff in the specialized outpatient clinics. A total of approx. 45 ml of blood (approx. 3 tablespoons) will be drawn and analyzed in a routine laboratory.

The following routine parameters are of particular interest for this study: differential blood count, CRP, IL-6, fasting blood glucose, HOMA index, cholesterol, HDL, LDL, triglycerides, ALT, AST, GGT, creatinine, urea, electrolytes, uric acid, vitamin D, ferritin, homocysteine, vitamin B12

### Statistics

#### Data Analysis and Evaluation

The quantitative data collected in this study will be analyzed using IBM SPSS. First, a descriptive data description will be carried out, calculating mean, standard deviation and percentiles to present the basic characteristics of the sample and the measured variables. To analyze changes in parameters over the course of treatment, both paired t-tests and repeated-measures analyses of variance (ANOVA) will be used. These procedures make it possible to assess differences between measurement time points (e.g., baseline vs. follow-up) and to reveal possible effects of the interventions. Prior to conducting these tests, normal distribution of the data will be examined, for example using the Kolmogorov–Smirnov test or the Shapiro–Wilk test.

In addition, relationships between variables will be examined using correlation analyses. Depending on data distribution, either the Pearson correlation coefficient (for normally distributed data) or the Spearman correlation coefficient (for non-normally distributed data) will be applied. Error probabilities of  $p < 0.05$  will be considered statistically significant. To investigate specific group comparisons and further detailed questions, post-hoc analyses may also be conducted.

The qualitative data from the patient satisfaction questionnaires will be evaluated by frequency analyses and a thematic analysis to identify common themes and key aspects of satisfaction. These complement the quantitative results and provide a more comprehensive insight into the patient perspective.

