## **Objectives and Hypotheses**

This pilot study aims to conduct an initial evaluation of the Specialized Outpatient Clinic for Nutrition and Mental Health and to evaluate other specialized clinics with innovative care concepts within our department. Initial data on treatment outcomes and patient satisfaction will be collected and analyzed. The findings will be used to identify and implement targeted optimization potential in patient care.

The central research question of this study is: Can continuous care in Europe's first Specialized Outpatient Clinic for Nutrition and Mental Health achieve a statistically significant reduction in stress levels in patients with psychosomatic disorders after one year of treatment? Is there also an influence on stress levels in our other specialized outpatient clinics?

As part of the individually tailored interventions aimed at nutrient supply, nutrition, the gut-brain axis and relationship-based medicine, we expect a significant reduction in patients' stress symptoms.

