## **Study Design**

This study will be conducted at the Clinical Department of Medical Psychology, Psychosomatics and Psychotherapy as a single-center, prospective pilot study.

Patients will be referred by private psychiatrists and/or general practitioners, as well as by colleagues from internal medicine (cardiology/gastroenterology/hepatology). Recruitment takes place during the initial consultation in the specialized outpatient clinic. Patients are informed about the possibility of participation when registering at the clinic desk and receive the information sheet so that they can read it independently before the consultation. During the initial consultation, patients are again comprehensively informed about the study by the physicians. Participation is voluntary and requires written informed consent.

Participants will complete questionnaires at baseline and subsequently at three-month intervals for one year. Laboratory tests will be performed during regular follow-up appointments in the clinic, which also take place every three months. The questionnaires will be completed online using the EvaSys system. A link will be sent to participants by email.

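### Interim vitamin D changes are compared across seasons with no season term: added noise under the planned even intake, and bias in the mean only if entry or drop-out is uneven over the calendar year

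*Protocol*

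**What the plan says.** Vitamin D is among the blood parameters under Secondary Outcome Measures and again under Standard Laboratory ("electrolytes, uric acid, vitamin D, ferritin, homocysteine, vitamin B12"). On timing, Standard Laboratory says: "Blood samples will be taken at baseline and then every three months during the regular follow-up appointments". The care is described under Objectives and Hypotheses as "individually tailored interventions aimed at nutrient supply, nutrition, the gut-brain axis and relationship-based medicine", so a nutrient level is a natural thing to report.

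For change over treatment, Data Analysis and Evaluation states that "both paired t-tests and repeated-measures analyses of variance (ANOVA) will be used". It then gives the reading: "These procedures make it possible to assess differences between measurement time points (e.g., baseline vs. follow-up) and to reveal possible effects of the interventions". The same section plans Pearson or Spearman correlations between variables. No control group is described, and no time point is singled out for the blood parameters.

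Patients enter one at a time, at their first consultation (Study Design). Considerations on Sample Size assumes a constant intake for the nutrition clinic of about 10 new patients per month, 120 per year, of whom 70% take part. No recruitment start or end date is given.

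**The concern.** Vitamin D status depends on sunlight. With three-monthly sampling, a patient's values at months 3 and 9 lie a quarter of a year out of phase with baseline, and the month-6 value lies half a year out of phase. The named tests compare these visits as if calendar time had no effect, and without a control group nothing else separates season from care. The five-visit ANOVA pools the out-of-phase visits with the one that matches.

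At stake is the reading of an interim change in vitamin D. If season moves the group mean, part of a rise or fall would be credited to the clinic or would mask a real change. If season does not move the mean, it still widens the interim comparisons and weakens correlations that involve vitamin D.

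**Working it through.** **Inputs from the protocol.** Blood at months 0, 3, 6, 9 and 12; rolling entry; constant intake. The projected number reproduces: 10 × 12 = 120, and 120 × 0.70 = 84.

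**Assumption.** The protocol gives no seasonal figure. I take a sinusoid with a 12-month period and half-swing A = 10–15 nmol/L. Results are in units of A first, so that another value can be put in.

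**Seasonal part of one patient's change.** Let θ be the phase at entry, measured from the yearly trough, so the seasonal level is −A cos θ.
- Month 6 minus baseline: 2A cos θ.
- Month 3 minus baseline: A(cos θ + sin θ).
- Month 9 minus baseline: A(cos θ − sin θ).
- Month 12 minus baseline: 0.

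**Even entry over 12 months, as the protocol assumes.** The mean of cos θ and of sin θ is 0, so the seasonal shift in the group mean is 0 at every visit. The spread is not zero:
- Month 6: SD = 2A/√2 = 1.41A, or 14.1–21.2 nmol/L. Divided by √84 = 9.17, the standard-error component is 1.5–2.3 nmol/L.
- Months 3 and 9: SD = A, or 10–15 nmol/L. Divided by 9.17, it is 1.1–1.6 nmol/L.
- Month 12: none.

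These components add in quadrature to the rest. For scale only, suppose the non-seasonal SD of change were 25 nmol/L (also assumed). The month-6 standard error would rise from 25/9.17 = 2.7 to √(625 + 200)/9.17 = 3.1 with A = 10, or √(625 + 450)/9.17 = 3.6 with A = 15.

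**Entry that does not cover whole years.** For even entry over L months centred on the trough (the worst case), the mean of cos θ is sin(πL/12)/(πL/12). The month-6 shift is 2A times its absolute value.

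| Entry | Mean of cos θ (absolute) | Month-6 shift | With A = 10–15 nmol/L |
|---|---|---|---|
| 6 months | 0.637 | 1.27A | 13–19 |
| 8 months | 0.413 | 0.83A | 8–12 |
| 12 months | 0 | 0 | 0 |
| 18 months | 0.212 | 0.42A | 4–6 |
| 24 months | 0 | 0 | 0 |

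**Twelve-month entry with uneven intake.** With intake proportional to 1 + 0.2 cos θ (±20%), the mean of 2A cos θ is 2A × 0.2 × ½ = 0.20A, or 2–3 nmol/L. Drop-out that depends on season acts in the same way.

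**Correlations.** Even entry adds seasonal variance A²/2 to each vitamin D value. If σ is the non-seasonal SD, a correlation with a non-seasonal variable is multiplied by σ/√(σ² + A²/2), so it is diluted. If the other variable also varies with season, the correlation is confounded. The protocol gives no σ, so I put no number on this.

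**The case against.** The strongest reply is that the protocol's own recruitment picture removes the bias. Entry is rolling, intake is taken as constant, and volumes for the other two clinics are also counted over a full year. Every visit then spans all seasons and the mean shift is zero. The remaining noise is already in the SD that a paired t-test uses, so that test stays valid and only loses precision. This stands. A reader might infer from the visit spacing that the interim means are biased as planned, or that shifts of 8–19 nmol/L are to be expected. The protocol supports neither, because it plans no six- or eight-month window. It does not exclude one either: constant intake is a feasibility estimate resting on January to August counts (91 first consultations), and no recruitment window is fixed.

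The second reply is that a season term for one of about 20 laboratory parameters belongs in a statistical analysis plan, which may exist unseen. Its absence alone is indeed no finding. But the protocol does name the methods and does say that they serve "to reveal possible effects of the interventions". The point is that a better method than the one named is available for this variable.

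A reader might also extend the point to diet, since "Food Frequency Items are recorded both at baseline and at follow-ups to document dietary changes and compliance with dietary recommendations". The protocol gives no basis for a seasonal size in those items, and their interim values serve to follow compliance. I make no claim about them.

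**Conclusion.** A minor point, limited to vitamin D. Under the planned intake there is no seasonal bias in the mean. There is avoidable noise, with a standard-error component of about 1.5–2.3 nmol/L at month 6 and 1.1–1.6 at months 3 and 9, and dilution of vitamin D correlations. Bias in the interim means is conditional on entry that is uneven or not in whole calendar years, or on seasonal drop-out. At month 6 it then ranges from about 2–3 nmol/L (±20% swing in intake) to 13–19 nmol/L (six-month entry in the worst season).

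All nmol/L figures scale with the assumed A. The standard errors also assume 84 patients with no losses, and the zero at month 12 assumes that visits keep to schedule.

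A reader might infer that the primary result is touched. It is not: the primary outcome is the stress score, with the hypothesis set at one year, where baseline and follow-up share a season. The wider weakness is reading any uncontrolled before-after difference as a possible effect of care; season is one part of that, and a removable one.

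**What to change.** In Data Analysis and Evaluation, for vitamin D:
- Make baseline to month 12 the main change contrast.
- Analyse months 3, 6 and 9 in a linear mixed model with visit plus one sine and one cosine term (12-month period) for sampling date, in place of the paired t-test and repeated-measures ANOVA.
- Adjust associations between vitamin D and other variables for the same two terms.

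The cost is a mixed model with two extra terms instead of the simpler tests, and the sampling date must be kept in the analysis file. No visit, sample or patient is added. The model can separate season from visit because entry is staggered. If entry proved very short, that separation would be weak and the month-12 contrast would have to carry the result. The adjustment also assumes one common seasonal curve, so differences between patients in seasonal swing stay in the residual.

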#### **Expected results:**

A reduction in subjective stress perception and an improvement in psychological well-being as well as quality of life are expected. Positive changes in physiological parameters, particularly inflammatory markers, are also anticipated, suggesting a supportive effect of nutrition-based interventions on psychosomatic health.

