## **Hypotheses**

The null hypothesis of the study is: There is no statistically significant reduction in stress levels in patients with psychosomatic disorders after one year of treatment in the specialized outpatient clinics of our department.

The alternative hypothesis is: After one year of treatment in the Specialized Outpatient Clinic for Nutrition and Mental Health, there is a statistically significant reduction in stress levels in patients with psychosomatic disorders in the specialized outpatient clinics of our department.

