### **Outcome Measures**

#### **Primary Outcome Measures**

- Target parameter for the primary hypothesis is subjective stress perception (PSS score)

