### **Limitations and Challenges**

This pilot study has some limitations and challenges that must be considered when interpreting the results.

First, the study duration may be too short to observe statistically significant effects or lasting changes, as the effects of nutritional and psychological interventions often take longer to fully develop. Second, the study is limited to a small number of participants in the specialized clinic, which may reduce statistical power and thus the likelihood of detecting significant results. This increases the risk of a Type II error, in which true effects are not recognized as significant due to insufficient power.

Another potential issue is the use of self-report measures (questionnaires), which are susceptible to biases such as social desirability or recall effects and can thus impair the reliability and validity of the data collected. In addition, compliance with specific therapeutic recommendations in the specialized clinics, such as dietary recommendations, is difficult to control, and individual differences in nutrient intake and utilization could influence the results of this study and lead to increased variability that occurs independently of the intervention. Due to financial and logistical constraints, it is not possible within the scope of this study to conduct more specific nutritional diagnostic tests that would allow for even more precise tailoring of interventions. These limitations affect the significance and generalizability of the results but at the same time indicate important starting points for future studies. These could include a larger sample size, longer follow-up periods and a more differentiated nutritional diagnostic approach.

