### **Summary**

This pilot study aims to investigate the effectiveness of treatment and overall patient satisfaction in Europe's first Specialized Outpatient Clinic for Nutrition and Mental Health as well as in other specialized clinics with innovative care concepts

(psychocardiology/psychohepatology). The study uses a single-center, prospective design and collects both subjective (questionnaires) and objective (blood values) parameters. The results of this study will help to improve patient care in a targeted manner and to collect initial data on the effectiveness of clinically hitherto little-tested nutrition-specific interventions in psychosomatics.

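### An uncontrolled before-after change can test the stated hypothesis but cannot be attributed to the interventions, as several sections of the protocol do

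*Protocol*

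**What the plan says.** Protocol, Study Design, sets the study up "as a single-center, prospective pilot study". No control arm, waiting list, randomisation or external comparator appears anywhere in the document. Participants are newly referred patients, measured at entry and every three months for a year.

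Protocol, Hypotheses, gives the alternative hypothesis that after one year "there is a statistically significant reduction in stress levels in patients with psychosomatic disorders in the specialized outpatient clinics of our department". The primary outcome is the PSS score. For change over time, Data Analysis and Evaluation says that "both paired t-tests and repeated-measures analyses of variance (ANOVA) will be used", at p < 0.05, and describes one purpose of these tests with the words "and to reveal possible effects of the interventions".

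Other sections go further:

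- **Introduction, Discussion and Summary** name effectiveness as something the study examines or informs. The Summary says the results will help to "collect initial data on the effectiveness of clinically hitherto little-tested nutrition-specific interventions".
- **Expected results** reads the anticipated changes as "suggesting a supportive effect of nutrition-based interventions on psychosomatic health".
- **Scientific Background** and **Objectives and Hypotheses** put the question causally: how dietary interventions act on symptoms, and whether care in the clinic can bring stress down.

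Limitations and Challenges covers study duration, small numbers, self-report bias, compliance, individual variability in nutrient intake and use, and the lack of more specific nutritional diagnostics. On inferential error it says: "This increases the risk of a Type II error, in which true effects are not recognized as significant due to insufficient power".

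**The concern.** A paired test compares the mean change with zero. Everything that moves a score over twelve months enters that change: treatment, the natural course of the complaint, other therapy or medication, and regression to the mean if patients enter care when their stress is above its usual level. Without a comparator these cannot be separated. Medication is recorded (Questionnaires), but the protocol describes no use of it in the analysis of change, and adjusting for it would not replace a control group.

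A significant fall in PSS is therefore compatible both with a helpful intervention and with none. As the aims and expected results are worded, a reader could take it as support for nutrition-based care. The limitations section, where such a reader should be warned, names the risk of missing a true effect but not the risk of a significant change without any treatment effect.

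**Working it through.** **1. The protocol's own figure.** Considerations on Sample Size expects about 10 new patients a month in the nutrition clinic and 70% participation: 10 × 12 = 120, and 120 × 0.70 = 84. The figure reproduces. It is an enrolment forecast for one clinic, not a power calculation and not a count of patients with a 12-month value.

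**2. Inputs that the documents do not give.** The PSS standard deviation, baseline level and 12-month retest correlation are absent, and there is no PSS entry threshold. Assumptions for illustration: equal SD at both times; retest correlation r between 0.5 and 0.8; patients enter on average k SD above the level to which they return; treatment effect zero; two-sided 5% test (the protocol does not state sidedness).

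**3. Formulas.**

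- Expected fall = k(1 − r) SD.
- SD of the change = √(2(1 − r)) SD.
- Standardised change dz = k√((1 − r)/2).
- Chance of a significant reduction: upper tail of the noncentral t with n − 1 degrees of freedom and noncentrality dz√n.

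At n = 84, an observed mean fall of 0.217 SDs of the change is enough for p < 0.05.

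**4. Worked case.** For k = 0.5 and r = 0.7, the fall is 0.5 × 0.3 = 0.15 SD, the SD of the change is √0.6 = 0.775, and dz = 0.15/0.775 = 0.194. The chance of a significant reduction at n = 84 is 42%.

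**5. Chance of a significant reduction with zero treatment effect, n = 84.**

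| Entry above usual level (k) | r = 0.8 | r = 0.7 | r = 0.6 | r = 0.5 |
|---|---|---|---|---|
| 0.25 SD | 11% | 14% | 17% | 20% |
| 0.5 SD | 30% | 42% | 53% | 62% |
| 0.75 SD | 58% | 75% | 86% | 93% |
| 1.0 SD | 82% | 94% | 98% | 99.5% |

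With no selection (k = 0) it is about 2.5%, the nominal rate in that direction.

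**6. Cross-check by simulation.** If patients enter only from the upper half of the baseline distribution, the chance at n = 84 runs from 67% (r = 0.8) to 98% (r = 0.5).

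**7. Sensitivity to n.** With 59 paired values (an assumed loss of about 30%), the 42% and 86% become 31% and 72%. With 42 (half of 84), they become 23% and 57%. Pooling all three clinics would raise them.

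**8. Hypothesis beside interpretation.** The Hypotheses section asks only whether stress is lower after a year, and a paired test answers that. Expected results, Discussion, Data Analysis and Evaluation, and Summary attach the change to the interventions or to effectiveness. Nothing in the design supports that second step.

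**The case against.** The best defence is that this is a self-described pilot with modest language. The Introduction also states an aim of documenting changes before and during care, the statistics section speaks only of possible effects, the Summary of initial data, and the Discussion of a basis for further research. A single-arm design is acceptable for such a study, and the formal hypothesis is one that the chosen tests can address. All of this stands, and it confines the point to interpretation and limitations. It does not remove the effectiveness wording or the nutrition-specific reading, and the hedges do not tell the reader what the design cannot separate.

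Several stronger readings are tempting but unsupported:

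- **That the limitations warn only of false negatives.** They also name self-report bias, including social desirability, which can produce apparent improvement.
- **That comparison between clinics is ruled out.** Data Analysis and Evaluation allows post-hoc group comparisons. No clinic contrast is specified, but such detail may sit in an analysis plan not shown here.
- **That patients are known to enter at a peak of distress.** Study Design says who refers them, not in what state, and some may come because of chronic heart or liver disease. Selection at a high point is an inference.
- **That a significant result will be reported as effectiveness.** No section commits the sponsor to this; the wording merely invites it.

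**Conclusion.** The point holds as a fault of interpretation in the protocol text. The design can establish a change in PSS during a year of care. It cannot attribute that change to the interventions, still less to nutrition, and the sections that do so should be corrected. The limitations section omits the main alternative explanations.

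The size is illustrative. With zero treatment effect and 84 pairs, regression to the mean alone gives a significant reduction in 11-20% of studies under weak selection (0.25 SD, r from 0.8 to 0.5), 42% at 0.5 SD and r = 0.7, and 86% at 0.75 SD and r = 0.6. It is about 2.5% without selection, and at a given level of selection it falls with fewer 12-month completers. These figures rest on assumed values of k and r, so they show that regression to the mean could produce the expected result, not that it will. A reader might infer that a false claim of effectiveness is a larger risk than a missed effect; the documents give no basis for ranking the two. The single-arm design and the paired test are not themselves at fault.

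**What to change.** 1. In Introduction, Expected results, Discussion, Data Analysis and Evaluation, and Summary, replace the effectiveness and intervention-effect wording with *change during care*. Reword the causal phrasing in Scientific Background and in Objectives and Hypotheses to match. State once, plainly, that a significant reduction will not be taken as evidence of effectiveness or of a nutrition-specific effect.
2. In Limitations and Challenges, add the absence of a control group as a main limitation, with regression to the mean, natural course and concurrent treatment as alternative explanations for any improvement.

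A clinic-by-time comparison should not be used to rescue a nutrition-specific statement. The clinics serve different populations, which may regress by different amounts, and the hepatology clinic itself gives lifestyle counselling (Scientific Background). If such a comparison is reported, label it descriptive.

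The cost is a revision of protocol wording. No procedure, outcome or primary test changes. The price is a more modest headline claim.

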#### **Introduction:**

This prospective pilot study examines the effectiveness of care and patient satisfaction in Europe's first specialized outpatient clinic that focuses on the influence of nutrition on mental and psychosomatic health. In addition, other specialized outpatient clinics of our department, in particular the clinic for psychocardiology and for psychohepatology, will be evaluated. The aim of the study is to document and assess changes in patients' subjective perception of stress and in their mental health before and during care over a period of one year. Furthermore, potential associations between psychological well-being and specific nutrition-related as well as physiological parameters will be investigated.

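### The association aim rests on ordinary Pearson/Spearman correlations with no stated unit of analysis, although stress, diet and blood are each measured up to five times per patient; a within-patient model is a cheap improvement

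*Protocol*

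**What the plan says.** The Introduction sets an association aim: "potential associations between psychological well-being and specific nutrition-related as well as physiological parameters will be investigated". The only method given for it is in Data Analysis and Evaluation, where "relationships between variables will be examined using correlation analyses" and, depending on distribution, "either the Pearson correlation coefficient (for normally distributed data) or the Spearman correlation coefficient (for non-normally distributed data) will be applied". Results with p < 0.05 "will be considered statistically significant".

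The variables concerned are repeated:
- Questionnaires, including the PSS (Study Design): "Participants will complete questionnaires at baseline and subsequently at three-month intervals for one year".
- Diet (Questionnaires): "Food Frequency Items are recorded both at baseline and at follow-ups to document dietary changes".
- Blood (Standard Laboratory): "Blood samples will be taken at baseline and then every three months during the regular follow-up appointments".

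Baseline plus months 3, 6, 9 and 12 gives up to five PSS–marker pairs per patient. Paired t-tests and repeated-measures ANOVA are named for changes in parameters over the course of treatment. No repeated-measures method is named for associations, and normality is the only criterion for choosing the coefficient.

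**The concern.** The usual p-value of a Pearson or Spearman coefficient needs independent pairs, and pairs from the same patient are not independent. The protocol therefore names a test family that fits the data only after they are reduced to one pair per patient, and it does not say how that is to be done. Three readings fit the text: all visits pooled, one wave at a time, or patient-level change scores. They differ in validity, in the question answered and in power.

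At stake is what the study can say about stress and markers. A pooled test would overstate the evidence. A single-wave test shows whether patients with higher marker values report more stress, not whether the two move together in a patient. Change scores do address joint movement but leave out the three middle waves. A schedule of five linked measurements supports a sharper analysis than any of these.

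**Working it through.** **Inputs.** The protocol expects 10 new patients a month in the nutrition clinic and 70% participation: 10 × 12 × 0.70 = 84, which reproduces its figure. Waves: up to k = 5. Considerations on Sample Size cites 2.5 to 3 contacts per patient and year in comparable settings (used there for psychocardiology), and blood is drawn only at routine visits, so k = 3 is also shown. The protocol gives no ICC. I assume the same ICC for both variables, 0.4 to 0.8, and two-sided tests at 5%.

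**1. Visits pooled, no true association.** The variance of r is inflated by D = 1 + (k − 1) × ICC², and the actual error is 2 × [1 − Φ(1.96/√D)].

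| ICC | D, k = 5 | Error, formula | Error, simulated | D, k = 3 | Error, formula |
|---|---|---|---|---|---|
| 0.4 | 1.64 | 12.6% | 12.5% | 1.32 | 8.8% |
| 0.6 | 2.44 | 21.0% | 22.2% | 1.72 | 13.5% |
| 0.8 | 3.56 | 29.9% | 30.1% | 2.28 | 19.4% |

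At ICC 0 there is no inflation. Spearman behaves like Pearson (21.2% simulated at ICC 0.6, k = 5). The number of patients does not enter D, so a larger sample does not help: with an assumed 180 patients, simulation gave 19.6% at ICC 0.6.

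**2. One pair per patient.** At n = 84 and k = 5, simulated error was 4.2–5.5% for a single wave and 4.5–5.5% for baseline-to-last change scores. Both are valid.

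**3. What a single wave measures.** Take ICC 0.6, a between-patient correlation of 0.4 and none within patients. The single-wave correlation is 0.4 × 0.6 = 0.24. Fisher's z gives 0.245 × √81 = 2.20 and power of about 60% (simulated 59–61%), while a within-patient test is significant in 5%. A significant single-wave result is thus quite compatible with no joint change at all.

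**4. Power for joint change.** Take ICC 0.6, a within-patient correlation of 0.2 and none between patients, n = 84.
- Single wave: r = 0.2 × 0.4 = 0.08; 0.0802 × √81 = 0.72; power 11% (simulated 10–11%).
- Change score, month 0 to 12: r = 0.2; 0.2027 × √81 = 1.82; power 45% (simulated 44–46%).
- Within-patient model, five waves: 84 × 4 = 336 within-patient degrees of freedom, so about 0.2027 × √334 = 3.70; power 96% (simulated 95–96%).
- Within-patient model, three waves: 0.2027 × √166 = 2.61; power 74% (simulated 73%).

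**5. Serial correlation.** The within-patient figures assume equal correlation between all visits. If neighbouring visits are more alike (AR(1) of 0.6–0.7), a random intercept alone gave about 9–11% error in simulation. Patient-clustered robust standard errors brought it back to about 5–6%. Change scores stayed at 4.6% under AR(1) 0.7.

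**The case against.** The strongest reply is that the protocol nowhere plans to pool visits, and that the choice of values entering a correlation is a detail a SAP commonly settles. A reader might infer that the trial is set to produce many false associations. The text does not support that: the 12–30% describes one reading of a silent passage and depends on ICCs the protocol does not give. Five pairs is also a maximum.

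A reader might also infer that every way of running the plan is poor. That is not so either. Correlating change scores fits the wording, keeps the 5% error and addresses joint change; at a within-patient correlation of 0.4 it had 97% power in simulation. Against the mixed model, what remains is a loss of information.

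Third, one might read Expected results as promising that stress falls when a marker falls. It says "Positive changes in physiological parameters, particularly inflammatory markers, are also anticipated, suggesting a supportive effect of nutrition-based interventions on psychosomatic health", next to a separate expectation of lower stress. Those are mean changes, for which the protocol has the t-tests and ANOVA. The Introduction promises only associations, and a between-patient correlation is a legitimate answer to that.

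All three replies stand. What they leave is that the protocol does not keep silent on method: it names a test family chosen by distribution alone, and a SAP that followed it literally would contain no within-patient model, although the data are collected for one.

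**Conclusion.** A cheap improvement, minor to moderate. The named correlations are valid with one pair per patient, and the protocol should say that this is how they will be used. Pooling would raise the error to about 12–30% (five pairs, ICC 0.4–0.8), or about 14% at ICC 0.6 with three pairs. For joint change, a within-patient model roughly doubles the power of change scores (about 95% against 45%) under the assumptions of 84 patients, five complete waves, ICC 0.6 and a within-patient correlation of 0.2. With fewer waves, or a stronger association, the gain is smaller. These are secondary analyses in a pilot study, and the primary PSS comparison does not depend on them.

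**What to change.** In Data Analysis and Evaluation:
- State that visits will not be pooled in an ordinary correlation test. Keep Pearson/Spearman for one pair per patient, and say whether it is the baseline value or the change score.
- For repeatedly measured pairs, fit a mixed model of PSS on the patient's mean marker value (between-patient part) and the deviation from that mean (within-patient part). Include wave as a fixed effect, so that a shared time trend does not create an association, and a random patient intercept.
- Allow for serial correlation, by an AR(1) residual structure or patient-clustered robust standard errors.
- Base any statement that stress and a marker change together on the within-patient coefficient and its 95% confidence interval.

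Cost: one paragraph and slightly more analysis work. No new data are needed, and SPSS, which the protocol already names, has a mixed-model procedure. The results will be slopes rather than correlation coefficients.
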